# Specialised orthotic care to improve functioning in adults with neuromuscular disorders: protocol of a prospective randomised open-label blinded end-point study

**DOI:** 10.1136/bmjopen-2020-039683

**Published:** 2020-11-19

**Keywords:** neuromuscular disease, rehabilitation medicine, protocols & guidelines

## Abstract

**Introduction:**

People suffering from leg muscle weakness caused by neuromuscular disorders (NMDs) are often provided with leg orthoses to reduce walking problems such as increased walking effort, diminished walking speed, reduced balance and falls. However, evidence for the effectiveness of leg orthoses to improve walking in this patient group is limited and there is an absence of standardised practice in orthotic prescription. In 2012 a Dutch multidisciplinary guideline was developed aimed to standardise the orthotic treatment process in NMD. Although application of the guideline in expert centres (specialised orthotic care) seems beneficial regarding clinical effectiveness, larger studies are necessary to confirm results and investigate cost-effectiveness. Therefore, this study aims to examine the effectiveness and cost-effectiveness of specialised orthotic care compared with usual orthotic care in adults with slowly progressive NMD.

**Methods and analysis:**

A prospective randomised open-label blinded end-point study will be performed, in which 70 adults with slowly progressive NMD are randomly assigned to specialised orthotic care (intervention) or usual orthotic care (control). Outcome measures are assessed at baseline and at 3 and 6 months follow-up. The primary endpoints are gross walking energy cost (J/kg/m) assessed during a 6 min walk test and achievement of personal goals, measured with the Goal Attainment Scale. Secondary endpoints include walking speed, gait biomechanics, stability, physical functioning, falls and fear of falling, perceived fatigue and satisfaction. For the economic evaluation, societal costs and health-related quality of life will be assessed using cost questionnaires and the 5-Level version of EuroQol 5 Dimension, retrospectively.

**Ethics and dissemination:**

The study is registered in the Dutch trial register (NL 7511) and the protocol has been approved by the Medical Ethics Committee of the Academic Medical Center in Amsterdam. Results will be presented at national and international scientific conferences and disseminated through peer-reviewed journals and media aimed at a broad audience including patients.

Strengths and limitations of this studyA broad range of outcome measures, both objective and self-reported, will be collected, resulting in a unique dataset of both functional effects, underlying biomechanical working mechanisms and costs.The two primary outcome measures to evaluate functional effects include walking energy cost and achievement of personal goals measured with the Goal Attainment Scale, which is chosen as an additional primary outcome measure to capture the diversity of orthotic goals relevant to the individual.Evidence will be obtained in a large group of adults with different slowly progressive neuromuscular disorders, which increases the generalisability of results.An economic evaluation will be performed alongside the study to provide insights into the cost-effectiveness of specialised orthotic care versus usual orthotic care.To account for the expected variability in treatment components of usual orthotic care, which is a possible limitation that could complicate the identification of underlying mechanisms of action between treatments, the process of usual orthotic care will be extensively documented.

## Introduction

People with slowly progressive neuromuscular disorders (NMDs), such as postpolio syndrome and Charcot Marie Tooth disease, frequently suffer from leg muscle weakness.^1^ Leg muscle weakness will change the gait pattern,^2^ causing walking problems such as increased walking effort,^3 4^ diminished walking speed,^3 4^ pain,^5^ balance problems and falls.^6 7^ These walking problems may restrict the patients’ performance of daily physical activities^8^ and negatively affect their independency and quality of life.^8 9^ Due to the progressive nature of NMD, walking problems will gradually increase over time,^9^ which will further negatively affect physical mobility, independency and quality of life.

Leg orthoses are provided to reduce walking problems in people with NMD.^10^ A leg orthosis is an ‘externally applied medical device encompassing (part of) the leg and foot, used to modify the structural and functional characteristics of the neuromuscular and skeletal systems’.^11^ In general, an ankle-foot orthosis (AFO) is provided in case of distal leg muscle weakness, which often includes weakness of the foot dorsiflexors and plantarflexors.^10 12^ Accordingly, the AFO should support foot clearance during swing by restricting plantarflexion and compensate for plantarflexor weakness by restricting dorsiflexion during late stance.^10^ Knee-ankle-foot orthoses (KAFOs) are provided for (additional) proximal leg muscle weakness, particularly weakness of the quadriceps, to stabilise the knee joint during the stance phase of gait and allow safe weight-bearing.^10 13^

In previous research, various types of AFOs for calf muscle weakness^14^ and KAFOs for quadriceps weakness have been found to improve walking in people with NMD.^15^ However, the strength of the evidence is rather limited due to a lack of proper study designs, relatively small sample sizes, and heterogeneity in types of leg orthoses and control conditions studied. Accordingly, there is a lack of evidence-based and standardised guidance on the application of leg orthoses. Furthermore, many different types of leg orthoses are being prescribed in current orthotic practice in NMD, varying largely in orthotic properties and effectiveness, with both good and suboptimal treatment outcomes in terms of improving walking.^16 17^

In 2012, a Dutch multidisciplinary guideline for leg orthoses in adults with slowly progressive NMD was developed with the aim to standardise the treatment process and improve treatment outcomes.^18^ The guideline was developed according to proposed national and international frameworks^19–21^ and compromises the entire process of orthotic treatment in systematically divided steps, as well as treatment algorithms for the selection of leg orthoses. According to the guideline, the care need should be individually characterised in terms of the personal health problems, goals and gait deviations to be addressed, caused by the underlying impairments. Based on the care need, the orthotic goals should be defined and matched with the orthosis design. Gait training after delivery of the orthosis after is essential to maximise effectiveness.^22^ Finally, it is important to systematically evaluate the effectiveness as well as user experiences to ensure the functionality of the orthosis.^23^

At this moment, the guideline is not widely applied throughout the Netherlands, as it requires sufficient expertise of the multidisciplinary care team involved and facilities for advanced 3-dimensional (3D)-gait analysis and gait training. However, prescribing leg orthoses according to the guideline (i.e. specialised orthotic care) seems promising in terms of clinical effectiveness as recently shown in two uncontrolled trials.^16 24^ In individuals with calf muscle weakness due to NMD, individually stiffness-optimised AFOs have been shown to reduce walking effort to a much greater extent compared with AFOs prescribed in usual orthotic care.^24^ Furthermore, in polio survivors,^16^ the increment in walking effort with KAFOs prescribed in specialised orthotic care was reduced with 18% towards normative values, when compared with usual care KAFOs. At this moment, the effectiveness of leg orthoses prescribed within specialised orthotic care on functioning needs to be investigated in a larger group of individuals with slowly progressive NMD in comparison to usual orthotic care to strengthen evidence for the possible benefit.

While good-quality studies are needed to strengthen the evidence for the effectiveness of specialised orthotic care in NMD, it is also imperative to investigate whether the treatment is cost-effective, which is currently unknown. Since new and expensive orthotic devices increasingly become available, it is important to assess their associated costs.^25^ Also, at this moment, an important problem in usual orthotic care concerns the low compliance of patients wearing their devices,^26^ which in turn leads to an inefficient use of healthcare resources.^27^ Optimally matching orthoses with the personal needs and goals of the patient, according to the guideline, could lead to gains in clinical effectiveness and subsequently a higher compliance. In this respect, specialised orthotic care could improve the efficiency of (healthcare) resource, but this has not yet been investigated.

The aim of this study is to examine the effectiveness and cost-effectiveness of specialised orthotic care compared with usual orthotic care on functioning in adults with NMD. We hypothesise that specialised orthotic care is more effective in terms of reducing walking effort and achieving personal goals when compared with usual orthotic care. Furthermore, specialised orthotic care is expected to be cost-effective compared with usual orthotic care from a societal and healthcare perspective.

## Methods and analysis

### Study design

The study is designed as a randomised open-label blinded end-point study that is prospectively registered at the Dutch Trial Register under number NL7511. The trial protocol was developed according to the Standard Protocol Items: Recommendations for Interventional Trials guidelines^28^ (online supplemental file 1). Recruitment started in March 2019 and is foreseen to end at December 2021. Measurements are conducted at baseline (T1) and 3 and 6 months after orthotic treatment is given (T2 and T3, respectively). To determine the cost-effectiveness, an economic evaluation is performed alongside the study. An overview of the study design is shown in figure 1.

10.1136/bmjopen-2020-039683.supp1Supplementary data

**Figure 1 F1:**
[figure not shown]
Overview of the study design.

### Study population

We intend to include 70 adults with slowly progressive NMD (such as Charcot-Marie-Tooth disease, postpolio syndrome, inclusion body myositis or myotonic dystrophy) or peripheral nerve injury who have non-spastic leg muscle weakness. For eligibility, patients may or may not use an orthosis provided in usual care at the time of recruitment. Patients will be recruited from rehabilitation centres and hospitals throughout the Netherlands and through the Dutch Association for Neuromuscular Diseases. If a patient is willing to participate, a screening visit is planned. During the screening visit, written informed consent (online supplemental file 2) is obtained and the investigator, in close collaboration with a rehabilitation physician, will check the inclusion and exclusion criteria.

10.1136/bmjopen-2020-039683.supp2Supplementary data

Inclusion criteria are: (1) minimum age of 18 years, (2) weakness of the calf muscles (ie, Medical Research Council (MRC) scale^29^ score <5 or not being able to make a heel-rise on one leg >3 times) and/or weakness of the quadriceps (ie, MRC score <5) (3) experiencing walking problems such as increased walking effort, pain and/or impaired balance during standing and/or walking, (4) able to walk for 6 min at comfortable speed with or without assistive device (eg, cane, crutch, walker), (5) indicated for an orthosis based on physical examination and 3D gait analysis and (6) motivated to use an orthosis. An exclusion criterion is: (1) insufficient mastery of the Dutch language.

### Sample size

The sample size of this study is based on a power analysis of the expected differences in walking effort (defined as gross walking energy cost) and the achievement of personal treatment goals between the intervention and control group. According to previous studies,^16 17^ a difference in change in walking energy cost of 0.60 J/kg/m from baseline to 6 months post-treatment is expected between usual orthotic care and specialised orthotic care, where a difference of at least 0.45 J/kg/m is considered as clinical relevant.^3^ Based on an intention-to-treat analysis, alpha of 0.05, power of 80% and using an estimated correlation coefficient of the repeated measures of 0.76 and SD of 0.90 J/kg/m, 30 patients per treatment group are necessary. The goal is to include 70 patients allowing for a 15% drop-out. This sample size also allows the detection of 1 point difference in personal achievement goal scores (Based on an intention-to-treat analysis, alpha of 0.05, power of 80%, and using an estimated correlation coefficient of the repeated measures of 0.70).

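### The 30 per group at 80% power does not belong to the stated contrast (a 0.60 J/kg/m difference in change to 6 months); on the natural reading of the SD the mismatch is conservative

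*Protocol article*

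**What the plan says.** Under Methods and analysis, Sample size, the protocol article describes the effect behind the calculation as follows: "a difference in change in walking energy cost of 0.60 J/kg/m from baseline to 6 months post-treatment is expected". It then sets a smaller threshold of relevance: "where a difference of at least 0.45 J/kg/m is considered as clinical relevant". The remaining inputs are a 5% alpha, 80% power, a correlation and an SD, and the result follows directly: "using an estimated correlation coefficient of the repeated measures of 0.76 and SD of 0.90 J/kg/m, 30 patients per treatment group are necessary". Seventy patients are to be enrolled to cover 15% drop-out. The section names no formula and does not say whether 0.90 is the SD at one visit or the SD of the change.

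Two other sections bear on this. Randomisation and blinding places the T1 measurement before allocation. Statistical analysis plans a linear mixed model over T1, T2 and T3 for walking energy cost, adjusted for the stratification factor and for baseline scores.

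**The concern.** The effect is stated as a difference in change from baseline, and an SD and a within-patient correlation are both given. A statistician would combine these into an SD of change and would not arrive at 30. The 80% is then attached to a contrast that is not the one described.

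This matters for reading the result. As written, the section implies 80% power for 0.60 and therefore clearly less for 0.45, the difference that the protocol itself calls clinically relevant. If the power for the described contrast is materially different, a null or borderline result on this primary outcome would be judged against the wrong yardstick.

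**Working it through.** **Inputs, all from the Sample size section.** Difference δ = 0.60 (relevance threshold 0.45); SD = 0.90; r = 0.76; alpha 0.05, taken as two-sided because the sidedness is not stated; power 80%. Allocation is 1:1 (Randomisation and blinding). The general formula is n per group = 2 × (1.96 + 0.8416)² × V / δ², with (1.96 + 0.8416)² = 7.849 and V the variance of the quantity compared.

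**1. Reproducing the stated 30.** For the mean of T repeated measurements, V = SD² × [1 + (T − 1)r] / T.
- T = 3 (T1, T2, T3): V = 0.81 × 2.52 / 3 = 0.6804; n = 2 × 7.849 × 0.6804 / 0.36 = 29.7, so 30. This matches.
- T = 2 (T2, T3 only): V = 0.81 × 1.76 / 2 = 0.7128; n = 31.1. Power at 30 per group is 78.6% by normal approximation and 77.2% by t test.

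The T = 3 version assumes a group difference of 0.60 at all three visits. T1 precedes randomisation, so the expected difference there is zero. The formula also responds to the correlation in the opposite direction from a change score:

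| r | n, mean of three visits | n, change score |
|---|---|---|
| 0.76 | 29.7 | 16.95 |
| 0.90 | 33.0 | 7.1 |

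**2. The contrast the section names, with 0.90 as the single-time SD.**
- Change score: V = 2 × (1 − 0.76) × 0.81 = 0.3888, SD of change 0.624; n = 2 × 7.849 × 0.3888 / 0.36 = 16.95, so 17 (18 by t test).
- Adjusted for baseline, one follow-up: V = (1 − 0.76²) × 0.81 = 0.342, SD 0.585; n = 14.9, so 15 (16 by t test).

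**3. Power of 30 evaluable per group for that contrast.** The standard error for the change score is 0.624 × √(2/30) = 0.161.
- δ = 0.60: 0.60 / 0.161 − 1.96 = 1.77, power 96%.
- δ = 0.45: 0.45 / 0.161 − 1.96 = 0.835, power 79.8% (78.5% by t test).
- Difference detectable with 80% power: 2.80 × 0.161 = 0.45 (0.46 by t test).
- Baseline-adjusted (standard error 0.151): about 98% for 0.60 and 85% for 0.45, both by normal approximation.

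**4. A second route to about 30.** A change score powered on 0.45 gives 2 × 7.849 × 0.3888 / 0.2025 = 30.1. If this was the calculation, the target reported beside the result is the wrong one of the two.

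**5. If 0.90 were the SD of change.** V = 0.81; n = 35.3, so 36 (37 by t test). Power at 30 per group is 73.3% (71.9% by t test) for 0.60. The correlation then has no role.

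**6. Drop-out.** 60 / 0.85 = 70.6, against 70 stated, which is a rounding matter.

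**The case against.** The strongest reply is that 30 does come out of the stated inputs. The repeated-measures formula is a recognised one, uses every number given, suits a correlation described as one between repeated measures, and sits naturally beside a mixed model over T1, T2 and T3. Under randomisation the expected baseline difference is zero, so a 0.60 difference in change is also a 0.60 difference at follow-up. Using 0.60 in a between-group formula is therefore not wrong in itself. Nor is it an error that n rises with the correlation when follow-up visits are averaged: with T2 and T3 only, the result is 31.1, close to 30.

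Most of this stands, and it rules out calling 30 a slip of arithmetic. It does not make 30 the answer for the contrast described. The exact match needs baseline counted as an outcome visit carrying the effect, although T1 precedes allocation and baseline scores are an adjustment in the planned analysis. The two-visit version avoids that, but it ignores baseline altogether, whereas the section speaks of change from baseline.

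A second reply is that an article may leave the formula and the type of SD to the full protocol. That is fair for the omission alone. The point here is that the target, inputs and result printed together do not agree.

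**Conclusion.** The point holds as a minor one. The stated 30 per group and 80% power do not correspond to a 0.60 J/kg/m difference in change from baseline to 6 months. With 0.90 as the single-time SD, that contrast needs about 17 to 18 per group, and 30 evaluable per group give about 96% power for 0.60 and about 80% for 0.45.

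This rests on a two-sided 5% test, equal SDs at the two visits and 30 evaluable patients per group. It also rests on reading 0.90 as a single-time SD, which the article does not say but which is the only reading that uses the correlation. That the three-visit formula was used is an inference from the match.

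A reader might infer that the trial is underpowered, with about 72–73% for 0.60. The document does not support this, because that figure requires setting aside the stated correlation of 0.76. A reader might also infer that the inputs cannot give 30, or that the 80% is simply false. They can give 30 by a recognised formula, and on the natural reading 80% understates the power for 0.60. The mismatch is conservative.

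**What to change.** Keep 70 patients and reword the paragraph:
- State that 0.90 J/kg/m is the SD at a single time point, if that is so, and name the formula and the visits it uses.
- Report that 30 evaluable patients per group give about 80% power for a difference in change of 0.45–0.46 J/kg/m and about 96% for 0.60 by change score. The baseline-adjusted figures may be added.
- Only if 0.90 is in fact the SD of change, drop the correlation and state about 72–73% power for 0.60.

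The cost is one paragraph. Enrolment, visits and the planned analysis do not change.

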### Randomisation and blinding

After baseline measurement (T1), participants will be randomly assigned in a 1:1 ratio to receive specialised orthotic care (intervention group) or usual orthotic care (control group). The randomisation scheme will be computer generated in Castor (Castor EDC, Amsterdam, the Netherlands) and uses blocks of random sequences with variable sizes (2, 4 and 6). Patients will be stratified by disease severity defined as distal leg weakness versus (distal and) proximal leg weakness, respectively. Outcomes will be assessed by a blinded and independent assessor. When patients are informed of group allocation, they will be instructed not to reveal this to the outcome assessor.

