### Intervention

#### Specialised orthotic care

Patients in the intervention group will receive specialised orthotic care at an expert centre that has implemented the Dutch guideline for leg orthoses^18^ and has facilities for 3D gait analysis, gait training and fabricating custom-made leg orthoses. For the orthotic care process, protocols of the guideline will be used and treatment integrity checks will be performed to ensure compliance with the guideline.

First, the health problems and goals of the patient will assessed by means of an interview, questionnaires, physical examination and 3D gait analysis. Based on these assessments, the multidisciplinary care team will identify how the patients’ problems and goals are best matched to an orthotic solution. The desired level of functioning for the patient and the required orthotic functions will be described in a care plan. Accordingly, the orthosis will be custom fabricated by an orthotic technician. After delivery of the orthosis, instructions on use and maintenance will be given to the patient and, when indicated, the patient receives gait training supervised by an experienced physiotherapist. Finally, after 3 months of using the orthosis, experiences of the patient as well as the desired level of functioning and orthotic functions will be evaluated. When needed, the orthosis will be adjusted based on the evaluation. The provision process will be extensively documented for each participant individually by an investigator who is not blinded.

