#### Usual orthotic care

Participants in the control group will receive usual orthotic care from a rehabilitation physician at their regular care centre. Treatment can vary across centres and may include provision of orthopaedic shoes, provision of off-the-shelf or custom-made AFOs or provision of off-the-shelf or custom-made KAFOs according to the discretion of the practitioners and local policy of the centre. For participants who already use an orthosis at baseline, usual orthotic care will concern the provision of a new orthosis which may be identical of different from the orthosis being used. The provision process in the usual care centres will be extensively documented for each participant individually by an investigator who is not blinded.

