### Outcome measures

Relevant demographic variables, anthropometrics and clinical characteristics will be measured at baseline (T1). Clinical characteristics to be evaluated include: (1) manually assessed muscle strength of the left and right hip flexors and extensors, hip abductors and adductors, knee flexors and extensors, ankle plantar and dorsal flexors and ankle invertors and evertors, scored according to the MRC scale and (2) passive range of motion of the hip, knee and ankle joints (left and right). Furthermore, (3) occurrence of joint deformities and (4) impairments in sensory function will be evaluated.

Primary outcomes and secondary outcomes (described below) will be assessed at baseline (T1) and at 3 and 6 months after orthotic treatment (T2 and T3, respectively). Additionally, orthotic properties (such as type, weight, material and orthotic functions) and adverse events due to the use of the device (such as pressure sores, pain, muscle soreness) will be documented. The use of any medication during the study will be monitored at all measurement time points and documented in the cost questionnaires. All collected outcomes will be entered into a Castor database. An overview of all outcomes per measurement visit is given in table 1.

**Table 1 T1:** Overview of outcomes per measurement session

		Baseline	Follow-up	
		T1 measurement (screening)	T2 measurement (12 weeks after delivery)	T3 measurement (24 weeks after delivery)

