**Additional outcomes**				
Demographics	Intake	X		
Anthropometrics	Physical exam	X		
Muscle strength	Physical exam	X		
Joint passive range of motion	Physical exam	X		
Sensory function	Physical exam	X		
Orthotic properties	CRF	X†	X	X
Adverse events	CRF		X	X

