#### Gait biomechanics

Gait biomechanics will be assessed with a 100 Hz 12-camera 3D motion capture system (VICON MX V.1.3) and two adjacent 1000 Hz force plates (OR6-7; AMTI, Watertown, Marssachusetts, USA). Preparations include placement of reflective markers on the body according to the Plug-In Gait model. After a static calibration, participants will be asked to walk along a 12 m long walkway. Conditions that will be assessed include barefoot walking (T1), walking with the current orthosis if applicable (T1) and walking with the new orthosis (T2 and T3). Per condition, at least three valid trials will be used for analysis containing a clear stance phase on the force plate for both feet and full visibility of all markers during the gait cycle. Joint angles, net joint moments and joint powers around the hip, knee and ankle will be calculated per trial and averaged over three trials. Spatiotemporal gait parameters (such as step length and step width) and relevant kinematic and kinetic variables (such as maximal ankle dorsiflexion angle, peak ankle power, knee angle and knee moment at midstance, hip flexion angle and maximal hip, knee and ankle angle during swing and progression of the centre of pressure) will be obtained from these averaged data and used for analysis.

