## Ethics and dissemination

The study protocol was approved by the Medical Ethics committee of the Amsterdam UMC, location Academic Medical Center, ABR-number 67 268. The study is registered at the Dutch Trial Register (NL7511) and will be performed in accordance with good clinical practice guidelines. An independent monitor of the Amsterdam UMC will monitor the study multiple times during the conduction of the study. Aspects that will be monitored will include inclusion rate, trial master file, informed consent process, inclusion and exclusion criteria, randomisation, trial procedures, source data verification, safety reporting and closing and reporting. The investigator will be encouraged to maintain the blinding as far as possible and code breaks should only occur in exceptional circumstances. Important protocol changes will be recorded (a new protocol version number will be assigned) and reported to the Medical Ethics Committee. When patients sign their informed consent, they will receive a participant ID, which will be coupled to all the data collected. Forms will be stored in a locked cabinet to assure anonymity. Only persons involved in the study have access to these forms. Insurance has been taken out for participation of patients in the study. After completion of the study, positive as well as negative or inconclusive results will be submitted to a peer-reviewed journal and presented at national and international scientific conferences. The study data sets and codes of the data analysis are available on request. Furthermore, results will be disseminated through other media aimed at a broader audience including patients. Participants will be informed about the results of the study by means of a newsletter.

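### Assessor blinding is not secured for control patients whose device visibly differs, and the judgement-scored GAS is the outcome most exposed

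*Protocol article*

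**What the plan says.** All references are to the protocol article.

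- **Blinding claim.** The title describes a blinded end-point design. Randomisation and blinding says "Outcomes will be assessed by a blinded and independent assessor", with no outcome excepted.
- **Safeguard.** The same section says that once patients know their group "they will be instructed not to reveal this to the outcome assessor". Ethics and dissemination adds only that "The investigator will be encouraged to maintain the blinding as far as possible".
- **Device in view.** Gait biomechanics lists among its test conditions "walking with the new orthosis (T2 and T3". Outcome measures also has staff document "orthotic properties (such as type, weight, material and orthotic functions) and adverse events due to the use of the device", and Table 1 marks both items at T2 and T3. The person who records them is not named.
- **Intervention device.** Under Specialised orthotic care, "the orthosis will be custom fabricated by an orthotic technician".
- **Control device.** Under Usual orthotic care, treatment may include "provision of orthopaedic shoes, provision of off-the-shelf or custom-made AFOs or provision of off-the-shelf or custom-made KAFOs".
- **Unblinded role.** Both care sections have a non-blinded investigator document the provision process for each participant.
- **GAS.** Primary outcomes has GAS scored at T2 and T3 on six levels from −3 to +2. It refers to an investigator who both defines and scores the scale, and does not say whether this is the blinded, independent assessor.

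**The concern.** The safeguard and the procedures do not fit together. Asking patients to stay silent protects against disclosure in conversation. It does not protect against an assessor watching the patient walk in a device whose type carries information about the arm. As described, shoes or an off-the-shelf device can come only from usual care.

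This matters most for GAS. The scorer has to judge whether a personal goal was narrowly missed, met or exceeded, and neighbouring levels are separated only by words. A scorer who believes a patient is a control could, without intending to, settle on the lower level. That would favour the trial's stated hypothesis that specialised care achieves more personal goals. GAS is one of two primary outcomes, and the open-label design relies on the blinded end-point to contain this kind of bias. Walking energy cost is calculated from measured oxygen uptake, respiratory exchange ratio and speed, so it leaves much less room for scoring judgement.

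**Working it through.** The article gives no figure for the success of blinding, so there is no stated number to reproduce. The sample size has no bearing on this point, except that the total of 70 is used below to turn a share into a count.

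**Inputs**

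- Allocation 1:1 (Randomisation and blinding).
- Every intervention orthosis is custom fabricated (Specialised orthotic care).
- Control devices may be shoes, off-the-shelf or custom-made (Usual orthotic care).
- p = share of controls given shoes or an off-the-shelf device. The document does not give it, so the full range 0 to 1 is shown.
- Assumed: the assessor knows that intervention devices are custom-made, can tell custom from off-the-shelf on sight, and uses device type alone.

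**Formulas**

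1. Share of all patients identified with certainty as controls: 0.5 × p = p/2.
2. Share of all patients with a custom device: 0.5 + 0.5(1 − p) = (2 − p)/2.
3. Probability of intervention given a custom device: 0.5 ÷ [(2 − p)/2] = 1/(2 − p).
4. Best guess (control if shoes or off-the-shelf, otherwise intervention): right for all intervention patients and for a share p of controls, so 0.5 + 0.5p.

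**Results**

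| p | Identified as controls (p/2) | Of 70 patients (35p) | P(intervention given custom) | Best-guess accuracy |
|---|---|---|---|---|
| 0 | 0% | 0 | 0.50 | 50% |
| 0.10 | 5% | 3.5 | 0.53 | 55% |
| 0.25 | 12.5% | 8.75 | 0.57 | 62.5% |
| 0.50 | 25% | 17.5 | 0.67 | 75% |
| 0.75 | 37.5% | 26.25 | 0.80 | 87.5% |
| 1 | 50% | 35 | 1.00 | 100% |

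Device type reveals the arm completely only if no control receives a custom device (p = 1), and reveals nothing only if every control does (p = 0). In between, unmasking is one-sided: some controls are identified for certain, while a custom device only raises the odds of intervention.

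**Timing.** The order of tasks within a visit is not stated, so at T2 GAS may be scored before or after the device is seen. At T3 the order no longer settles the matter. If the same person scores GAS and attended the T2 gait test, that person has already seen the device.

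**The case against.** The strongest reply has four parts.

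- **Custom devices in controls.** Usual care may supply custom-made orthoses. Every patient must be indicated for an orthosis to enter, and controls who already use one are to receive a new orthosis. Shoes-only or off-the-shelf provision may therefore be uncommon, and p small. This stands: a reader might infer that assessor blinding is lost altogether, and the document does not support that.
- **Who records the device, and when.** A reader might also infer that the blinded assessor fills in the orthotic-properties form, or that GAS is scored after the walking tests. Neither is stated. An unblinded investigator already documents provision and may do this recording too, and visit order and staff tasks are commonly left to a full protocol. This also stands, and silence on these details is not the point. The point rests on what is stated: a safeguard limited to speech, a device worn at both follow-up gait tests, and device types that differ by arm.
- **A modest promise.** The design is declared open-label and blinding is to be kept only as far as possible. However, the title and the blinding section make the claim without qualification.
- **No demonstrated bias.** Nothing shows how far a scorer who guesses the arm would move a GAS score. That is correct. If identified controls were marked down by b levels on average, the control-arm mean would fall by p × b, and the document gives neither quantity. No bias estimate can be offered, and none should be read as a fraction of the 1-point difference in the sample size section.

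It also counts for the plan that goals are set at baseline, before randomisation, so goal definition is not affected.

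**Conclusion.** The concern holds in limited form. Blinding of the assessor is not secured for controls whose device visibly differs, because the only concrete safeguard does not cover what the assessor sees. From device type alone, best-guess accuracy is 0.5 + 0.5p, and p/2 of all patients are identified as controls. With p unknown, this runs from no unmasking to full unmasking, and no part of the range can be called expected. The figures assume an assessor who recognises the device type and knows what each arm can receive; a less informed assessor would do worse.

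GAS is the outcome at risk. Separately, the description of a single investigator who defines and scores GAS needs to be reconciled with the blinded and independent assessor. This weakens the protection of one co-primary outcome and should be corrected; it does not invalidate the design.

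**What to change.** Amend Randomisation and blinding, Outcome measures and Primary outcomes to state that:

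1. The GAS scorer at T2 and T3 is the blinded, independent assessor, with the wording on the investigator who defines and scores GAS brought into line.
2. At each follow-up GAS is scored and locked before any walking test, with the device out of sight. Where existing staffing allows, the scorer does not run the gait tests at either visit; otherwise what is seen at T2 carries over to T3.
3. Orthotic properties, device-related adverse events and the D-QUEST are collected by the unblinded investigator already in the trial.
4. The assessor records a guess of allocation after scoring GAS, so that the success of blinding can be reported.
5. Assessor blinding of the other judgement-based outcomes is described as partial.

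The cost is minor visit logistics and a reassignment of tasks. Recruitment began in March 2019, so visits already held under the previous arrangement must be flagged. Only later visits benefit. The change does not remove all bias from GAS, because patients know their allocation and this can still colour what they report.
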